### Study Design and Intervention Protocol

Our study consists of a 3-arm controlled trial with a parallel study design involving cognitively healthy older people. Participants are allocated into the Activ4Brain group and 2 control groups: an active control group engaged in AE alone and a passive control group, instructed to maintain their daily routines. The passive control group is included to control for the effect of test-retest. The AE group is included to assess if including cognitive training leads to a greater effect on cognition than AE alone and to control for the participants’ motivation to engage in the evaluation sessions, which might be decreased in passive control groups. The group allocation ratio is 1:1:1. The intervention consists of 24 sessions, held twice a week for 3 months. The participants are tested at baseline and after the 3-month training programs (Figure 1).

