### Participant Recruitment, Eligibility Criteria, and Sample Size

Participants are recruited from Portugal’s Coimbra District through personal communications, press releases, social media posts, and distribution of informative leaflets and posters. Recruited participants receive comprehensive information regarding data collection procedures, exercise protocols, and measures of protection of personal information procedures. Participants who volunteer to participate in the study are interviewed for eligibility and asked to sign an informed consent form.

Inclusion criteria are cognitively healthy men and women between 55 and 75 years of age, with a physical condition compatible with the practice of moderate AE. Exclusion criteria include any disability or health problem incompatible with moderate AE and objective cognitive impairment. The Physical Activity Readiness Questionnaire is used to screen contraindications for physical exercise. Before the intervention, we ensure participants’ fall risk is low using the Timed Up and Go (TUG) test [25].

Participants are instructed to continue any ongoing concomitant care. Details of the concomitant care received are recorded at baseline and, to assess any changes, at follow-up.

Sample size determination has been made using the G*power (version 3.1.9.7; written by Franz Faul, Universität Kiel, Germany) program. As reported in previous studies [26,27], we expect a small to moderate effect size of the Activ4Brain program on cognitive function (our primary end point). We calculated a sample size of 66 participants by setting Type I error (α) at 0.05, Type II error rate (1−β) at 0.95, and an effect size η^2^ of 0.06 (corresponding to an effect size *f* of 0.25, using the option for effect size specification as in G*Power 3.0) for repeated-measures ANOVA, within-between interaction, with 3 groups and 2 repeated measures. Accepting a dropout rate of 10%, 75 participants are recruited.

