### Statistical Analysis Plan

The study of the effect of the Activ4Brain program on the primary outcome (cognitive function) is confirmatory because we hypothesize, according to previous evidence, that the integrated cognitive-aerobic training program results in larger improvements than AE alone or no intervention (passive control) [47]. All other analyses are exploratory.

Continuous cognitive outcomes will be summarized descriptively with mean (SD) for each group and time. These variables will be analyzed with repeated-measures ANOVA with 1 between-subjects factor (group) and 1 within-subjects factor (time=preintervention vs postintervention). The Activ4Brain intervention will be considered effective in improving cognitive function if the group × time interaction is significant at a level of .05, if the post hoc tests (with CI adjustment using Bonferroni) show a significant effect of time for the Activ4Brain group, and the improvement is higher for this group than for the other control groups. If the data do not meet assumptions of sphericity, the Greenhouse-Geisser correction will be used. Description of the effect sizes by partial η^2^ will follow the following cutoff points: less than 0.06 will be considered a small effect; between 0.06 and 0.14 will be considered a medium effect; and higher than 0.14 will be considered a large effect [48].

Missing data will be assessed prior to analysis. Analyses will be conducted using the available data (complete case analysis), and participants with missing data for a specific outcome variable will be excluded only from the relevant analysis.

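### The success rule attaches no test or level to the comparison of Activ4Brain with aerobic exercise alone, so read literally a numerical edge over that arm is enough

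*Protocol article*

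**What the plan says.** The Statistical Analysis Plan section of the protocol article sets a three-part rule for each continuous cognitive outcome:

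1. The group × time interaction in a repeated-measures ANOVA (three groups, two times) is significant at .05.
2. Post hoc tests with Bonferroni-adjusted intervals find a significant time effect within the Activ4Brain group.
3. Improvement is greater in that group than in the controls.

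Parts 2 and 3 share one clause: "show a significant effect of time for the Activ4Brain group, and the improvement is higher for this group than for the other control groups".

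The same section calls the primary analysis confirmatory because the integrated program is expected to improve cognition more than AE alone or no intervention. The Discussion repeats that the comparison with AE alone will be treated as confirmatory. Study Design and Intervention Protocol gives each control arm its purpose: "The AE group is included to assess if including cognitive training leads to a greater effect on cognition than AE alone", and "The passive control group is included to control for the effect of test-retest".

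The sample size was computed for a "repeated-measures ANOVA, within-between interaction, with 3 groups and 2 repeated measures", which is the omnibus test.

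**The concern.** None of the three parts, read as written, requires statistical evidence that Activ4Brain improves cognition more than AE does.

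- **Part 1** is an omnibus test. It can be significant only because both exercise arms differ from the passive arm.
- **Part 2** is a pre-post test within one arm. Practice on repeated tests can satisfy it, and the passive arm was included to deal with exactly that.
- **Part 3** is the only part that refers to the controls. It says which group's improvement must be larger but not how that is to be shown. If Activ4Brain and AE are truly equal, coming out numerically ahead of AE is close to a coin flip.

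At stake is the question for which the AE arm exists. If exercise does all the work and cognitive training adds nothing, the rule can still be met, and the result would naturally be read as support for the confirmatory hypothesis.

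**Working it through.** **Inputs from the protocol (sample size section).** "setting Type I error (α) at 0.05, Type II error rate (1−β) at 0.95" (0.95 is taken as power); η² 0.06, "corresponding to an effect size *f* of 0.25, using the option for effect size specification as in G*Power 3.0"; "We calculated a sample size of 66 participants"; "Accepting a dropout rate of 10%, 75 participants are recruited". Allocation is 1:1:1, so 22 evaluable per arm.

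**Assumptions not in the protocol.** Pre-post correlation ρ = 0.5; normal change scores with equal variance, scaled to SD 1; practice gain 0.3 SD in every arm; Bonferroni over three tests for the within-arm time effect.

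**Step 1: reproduce the plan's figure.** Under the stated G*Power convention, λ = N·f²·m/(1−ρ), with df = 2 and N−3.

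- N = 66: λ = 66 × 0.0625 × 2 / 0.5 = 16.5, power 0.953.
- N = 63: λ = 15.75, power 0.944.

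So 66 is the smallest multiple of three that reaches 0.95. Dropout: 66/0.9 = 73.3, so 74, or 75 for three equal arms. Both stated numbers reproduce. At N = 66, power is 0.71, 0.86 and 0.998 for ρ = 0, 0.3 and 0.7.

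**Step 2: convert the powered effect to change scores.** λ = n·Σ(μᵢ − μ̄)²/SD², with n = 22.

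- Both exercise arms at d, passive at 0: 16.5 = 22 × (2/3)d², so d = √1.125 = 1.06.
- Only Activ4Brain at d: the same equation, d = 1.06.
- Graded effects 2e, e, 0: 16.5 = 22 × 2e², so e = √0.375 = 0.61, giving 1.22 / 0.61 / 0.

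**Step 3: simulate the rule when Activ4Brain and AE are equal.** Change scores, 22 per arm, one million trials per scenario, one outcome. The table gives the percentage of trials meeting each rule.

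| Common advantage over passive (SD of change) | Literal rule (part 3 = numerically highest) | Part 3 also tested with Bonferroni | Both contrasts at two-sided 0.05 |
|---|---|---|---|
| 0.1 | 2.6 | 0.2 | 0.8 |
| 0.2 | 4.6 | 0.3 | 1.1 |
| 0.3 | 7.7 | 0.4 | 1.5 |
| 0.5 | 18 | 0.7 | 2.1 |
| 0.7 | 32 | 0.8 | 2.4 |
| 1.06 | 48 | 0.8 | 2.5 |

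At 1.06 SD the interaction is significant in 95% of trials and the Activ4Brain time effect almost always, so the numerical ordering decides the outcome. About 95% of the declared successes then show no significant Activ4Brain-AE difference in change, even at an unadjusted 0.05. Setting the practice gain to zero at 1.06 SD leaves the rate unchanged at 48%.

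**Step 4: power when Activ4Brain is truly better, 22 per arm.**

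| True change, Activ4Brain / AE / passive | Literal rule | Both contrasts at 0.05 |
|---|---|---|
| 1.06 / 0 / 0 | 95% | 89% |
| 1.22 / 0.61 / 0 | about 93% | 51% |

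In the graded case the AE contrast is 0.61 SD. A two-sided 0.05 test of that contrast alone needs about 42 per arm for 80% power and 70 per arm for 95%.

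**The case against.** **Wording.** Parts 1 and 2 each have their own conditional and part 3 does not, so part 3 can be read as something the Bonferroni post hoc tests must show. Under that reading the rate stays below 1% in every scenario above and the defect disappears. This stands as a possible reading. But the sentence describes only the time effect as significant and names no contrast on change, so it does not settle the matter.

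**Label.** Meeting the rule earns the description effective for cognition, which matches the primary aim under Primary Outcomes. It is not worded as superiority over AE. This also stands. The link to superiority comes from the confirmatory hypothesis in the same section, the Discussion and the stated purpose of the AE arm.

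**Size of effect.** The Introduction describes exercise effects on cognition in the general population as small, and the sample size section expects a small to moderate effect for the whole program. Exercise-only effects of 0.7 or 1.06 SD are therefore the less likely end of the range. At 0.1-0.2 SD the literal rule is met in only about 3-5% of trials.

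**Several outcomes.** A reader might infer that the rates should be compounded across the five primary domains. That would measure multiplicity, a different question, and the document does not say that success on one domain is enough for an overall claim. The figures here are per outcome.

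**Remedy.** Data collection has ended with 73 enrolled, so the power lost by testing the AE contrast cannot be bought back. That is correct and belongs in the report.

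**Conclusion.** The rule is inadequately fixed on the trial's central comparison. It gives explicit significance requirements to the interaction and the within-arm time effect, and none to Activ4Brain versus AE.

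A reader might go further and infer that the plan definitely leaves the hypothesis untested, or that it will declare superiority over AE on a numerical edge. The document supports neither as a certainty: the wording allows a tested third part, and the rule's own conclusion is effectiveness rather than superiority.

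On the literal reading, the chance of meeting the rule when cognitive training adds nothing is about 3-8% per outcome for small exercise effects and 18-48% for effects of 0.5-1.06 SD of change. It is at most about 2.5% when both contrasts are tested. These rates rest on 22 per arm, equal-variance normal change scores and a 0.3 SD practice gain. Identifying 1.06 SD with the powered effect rests on ρ = 0.5.

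The ambiguity matters more because the Discussion acknowledges that the analysis plans were not specified before the data were acquired. The choice of reading should be fixed before results are seen by group.

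**What to change.** Replace the third part of the rule, for each outcome, with wording such as: the integrated program will be concluded better than AE alone only if the between-group contrasts on change, Activ4Brain minus AE and Activ4Brain minus passive control, are both significantly positive at two-sided 0.05.

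- No Bonferroni adjustment is needed between the two contrasts for this joint claim, because both must succeed.
- Report the within-arm time effect descriptively.
- Keep the two claims separate. If only the contrast with passive control is significant, conclude that the program is better than no training and say nothing about an advantage over AE.
- Give the date of the change and state that it followed data collection.

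The edit is one paragraph and needs no new data. The real cost is power, which the sponsor should disclose: the 66 participants were sized for the omnibus interaction, not for the AE contrast. At 22 per arm, power for the joint claim falls from about 95% to 89% if only Activ4Brain works, and from about 93% to 51% under graded effects. A non-significant AE contrast would then be inconclusive, not evidence that the two programs are equivalent.

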### Data Management and Monitoring Plan

A unique code will be attributed to each participant, and the data will be registered in databases separate from any identifiable information. For each stage of data collection, the validity and integrity of the collected data will be checked by at least 2 researchers. The researchers will validate data ranges and cross-check the entries in the databases.

Due to the trial’s short duration and minimal risks, there will be no requirement for a Data Monitoring Committee or interim analyses.

### Data Sharing

Twelve months after each publication of trial results, the deidentified individual participant data that underlie the published results will be made available indefinitely in a public repository (eg, Open Science Framework, OpenNeuro) to anyone who wishes to use the data for any purpose.

## Results

Data collection started in January 2024 and finished in April 2025. Seventy-three individuals (40 women and 33 men) were enrolled in the study and assigned to the 3 groups. The average age was 66 (SD 6) years. Data analyses are ongoing, with the publication of the results estimated for 2026 and 2027.

## Discussion

Enhancing the levels of physical and cognitive function of older people can have a significant effect on their quality of life. The Activ4Brain program aims to achieve this as a group-based AE program that incorporates targeted cognitive training and is designed to be fun and engaging and easily applicable in the community or in care institutions.

This study will allow us to determine if this program has a positive effect on the cognitive function of older people and compare its effectiveness with that of AE alone. Additionally, we will investigate the neurobiological mechanisms underlying the program’s impact on cognition by studying the associations between brain, autonomic, and physical function and inflammation and neuroprotective markers. Understanding these associations is essential to understand the mechanisms by which exercise and cognitive training may help preserve cognition and will contribute to the refinement and targeting of existing interventions [2]. Specifically, pupil-linked arousal responses and EEG measures of brain function will be used to elucidate the neurobiological mechanisms underlying cognitive changes. Engagement of pupil-linked arousal during exercise has been shown to correlate with improvements in cognitive task performance [49,50]. In fact, a single bout of exercise can change the engagement of the pupil-linked arousal system during cognitive tasks, leading to performance improvements [51]. Thus, engagement in regular exercise combined with cognitive training might change the way the pupil-linked arousal system is activated during cognitive task performance, and this might positively impact brain function and behavior. The data acquired within the scope of this study protocol will allow us to evaluate these hypotheses.

Neuroprotective and inflammatory biomarkers will be studied to investigate the neurobiological mechanisms of the effect of exercise and cognitive training on cognition, thus contributing to the understanding of muscle-immune-brain interactions. Aging-related increases in low-grade chronic inflammation, associated with immunosenescence, may lead to neurodegeneration and cognitive decline [52-55]. Circulating proinflammatory cytokines such as IL-1β, tumor necrosis factor-α, and IL-6 can activate microglia and astrocyte cells and elevate production of proinflammatory cytokines in the brain, which causes neuronal death and cognitive decline [56]. Exercise has anti-inflammatory effects [57-60], induces a decrease in proinflammatory monocytes, and causes an acute increase in muscle-secreted IL-6 that elevates the secretion of anti-inflammatory cytokines like IL-10 and IL-1RA [58]. Moreover, cognitive stimulation also decreases inflammatory cytokine levels in older populations [61]. Thus, the combination of exercise and cognitive stimulation may have synergistic benefits on the inflammatory profile.

One of the strengths of this intervention is that, unlike earlier exergaming and dual-task programs that rely on limited cognitive tasks or fixed difficulty, Activ4Brain targets 5 aging-sensitive cognitive domains, adapts task difficulty weekly to performance, and delivers cognitive training during exercise-induced arousal, in a socially engaging group format intended to support long-term adherence.

The retrospective nature of the publication of this protocol has the objective of providing a detailed description of the methods, ensuring that the information is available for trial replication. However, due to the inherent limitation associated with the fact that the publication of the protocol occurred after the end of data collection and the analysis plans presented were not specified before the data were acquired, the results from the study will be used mainly to generate new hypotheses for future clinical trials. Nevertheless, we expect that integrated cognitive and AE will have a stronger effect on cognition than AE alone [47], and we will treat this analysis as confirmatory. However, it is important to note that we are studying the effects of a novel intervention designed specifically for this study, and we do not have strong convictions regarding which specific cognitive domains will be most affected and which cognitive tests will best capture these effects, particularly when addressing cognitive decline in healthy older people. In fact, a large percentage of studies investigating the impact of this type of intervention on cognition use measures of global cognition such as the Mini-Mental State Examination or the Montreal Cognitive Assessment. These tests, while adequate to help diagnose mild cognitive impairment and dementia, suffer from ceiling effects in the cognitively healthy population [62]. To avoid this problem, this protocol includes measures of cognition more sensitive to subtle changes in cognitively healthy older adults.

Notably, it is possible that this type of intervention might be particularly effective in people with lower physical function and/or lower cognitive function who present a higher potential for improvement. In fact, there is evidence that age-related cognitive decline shows high variability, with some individuals aging better than others [63]. Future studies should explore the impact of the intervention focusing on populations with sedentary lifestyles, lower education levels, or poorer cognitive function.

Finally, the study was designed to include many outcomes aimed at studying not only the impact of the program but also the neurobiological mechanisms underlying its effects. However, the sample size was calculated to test only the primary outcome (cognitive function). This limitation results in all the other analyses being exploratory, so these results will not confirm the additional benefits of the Activ4Brain program but will rather contribute to the formulation of new hypotheses for future studies.

In conclusion, the Activ4Brain program offers a promising intervention that takes advantage of the known neurobiological impact of AE and cognitive training to potentiate their impact on cognition. The gamification of the computerized cognitive training tasks specifically designed to target relevant cognitive domains and the organization of the training in group classes has the potential to increase user motivation and long-term adherence, potentiating the program’s impact. The findings of this trial will contribute to our understanding of the best interventions to improve cognitive function in old age and will contribute toward our understanding of the neurobiological mechanisms underlying the impact of exercise and cognitive training on cognitive, brain, mental, and physical health.
